### Trial Design, Setting, and Participants

This is a cross-sectional exploratory single-session experimental study that will be laboratory based in Auckland University of Technology. A total of 40 adults will participate in the study (20 healthy adults and 20 adults with motion sensitivity after vestibular disorder). Healthy adults aged between 18 and 60 who are independently mobile and have no history of neurological conditions will be recruited through neurorehabilitation research team networks and community advertisements. Adults with motion sensitivity will be recruited through a specialized vestibular disorders clinic. They will be included if they have had a history of vestibular disorder (confirmed by a clinician in the vestibular disorder clinic) but have no current signs of acute vestibular deficits, are aged between 18 and 60 [40,41], have a history of motion sensitivity symptoms as reported by the Visual Vertigo Analogue Scale (score >5) [42-44], and score >40 on the Dizziness Handicap Inventory [44]. People with a history of previous eye surgery, or a medical condition that may influence eye movements such as sarcoidosis, Lyme disease, diabetes mellitus, traumatic brain injury, and migraine will be excluded from the study.

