### Statistical Analysis

#### Sample Size Calculation

There is a lack of experimental evidence in the population of interest to conduct a power calculation for the required sample size. It is unclear if factors such as age or gender affect visual fixations and there is minimal information on population variation. Therefore, an arbitrary sample size of 20 in each group has been selected. This has been selected in accordance with studies performed in adults with motion sensitivity [33,34]. The data from this study may help inform future studies for the required sample size.

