#### Analysis

Descriptive statistics (mean and standard deviation) will be calculated for each of the variables. Data normality will be examined using the Kolmogorov–Smirnov statistic. One-way independent-measures analyses of variance will be performed to investigate the differences between groups for all variables. Post-hoc analysis with Šidák adjustment will be used for multiple comparisons [48]. Finally, a receiver operating characteristic curve analysis will be applied to determine threshold values in gaze, COP, and COM parameters, allowing identification of the impairment induced by motion sensitivity. The optimal cutoff point will be determined using the Youden Index. Areas under the curve, specificity, and sensitivity will also be calculated. Values of areas under the curve will be categorized as follows: excellent (≥0.90), good (0.80-0.90), fair (0.70-0.79), and poor (<0.70).

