## Discussion

This is an exploratory study with the primary aim to identify whether fixational instability is associated with motion sensitivity and whether it leads to increased postural sway and altered kinematics in adults with motion sensitivity.

This study will provide a detailed investigation of visual fixations, postural sway, and kinematics in complex visual environments. The use of a mobile eye tracker device will investigate naturalistic eye behavior when exposed to experimental stimuli. The task hierarchy will help in understanding how characteristics of visual fixations change when a person views a complex visual environment as opposed to neutral environments. The experimental tasks might provoke symptoms in some participants; however, we expect that all participants will be able to complete the protocol with appropriate rest intervals between tasks. Our sample size of 20 participants in each group is a foundational step in exploring whether visual fixations contribute to motion sensitivity after vestibular disorder. We anticipate the outcomes will be able to detect a difference between healthy adults and those with motion sensitivity. Results from this study will inform future trials and will be used to inform development of diagnostic and rehabilitation programs.

We hope that this study will increase our understanding of the complex interactions of vision and balance in people with motion sensitivity. If we determine that gaze and postural control characteristics are altered, we will develop an intervention that is designed to re-align the gaze and postural control characteristics closer to those of the control population. This intervention would then be tested in a series of clinical trials to determine effectiveness.

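### Sensitivity and specificity at Youden cut-offs will be optimistic because cut-off and accuracy come from the same 20+20 people; a single AUC is imprecise, not biased

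*Protocol article*

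**What the plan says.** The Analysis section of the protocol article ends with an ROC step: "a receiver operating characteristic curve analysis will be applied to determine threshold values in gaze, COP, and COM parameters", which the same sentence says will allow the impairment caused by motion sensitivity to be identified. It continues: "The optimal cutoff point will be determined using the Youden Index", and "Areas under the curve, specificity, and sensitivity will also be calculated". The AUC is then graded in words: "excellent (≥0.90), good (0.80-0.90), fair (0.70-0.79), and poor (<0.70").

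The study enrols "20 healthy adults and 20 adults with motion sensitivity after vestibular disorder". Under Sample Size Calculation, "an arbitrary sample size of 20 in each group has been selected". The Šidák adjustment in the Analysis section is attached to post-hoc comparisons, not to the ROC step. The Discussion says that the results "will be used to inform development of diagnostic and rehabilitation programs".

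**The concern.** The Youden cut-off is the value at which sensitivity plus specificity is largest in the sample. Part of that maximum is chance. When sensitivity and specificity are read from the same sample, the chance part is reported as accuracy. With 20 people per group each person moves sensitivity or specificity by 5 percentage points (1/20), so the chance part is not small.

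The cut-off itself would also move a good deal in a repeat of the study. A reader who took the published threshold, sensitivity and specificity into a diagnostic programme would find lower accuracy in new people. Verbal grades on the AUC point value add to this, because at this sample size the sampling error is wider than a band.

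**Working it through.** **Inputs from the article.** Two groups of 20 (Trial Design, Setting, and Participants). Cut-off rule: maximum J, where J = sensitivity + specificity − 1 (Analysis). Parameters: 3 gaze (Visual Fixations), 3 COP (Postural Sway), and 3 COM measures × 2 segments = 6 (Kinematics), so at least 3 + 3 + 6 = 12. Six tasks (Experimental Tasks). The article states no accuracy, precision or power figure to reproduce.

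**Assumptions.** Normal outcomes with equal variance in both groups. True AUC 0.5 to 0.9, or a standardised difference d with AUC = Φ(d/√2), so d = 0.5, 0.8 and 1.2 give AUC 0.64, 0.71 and 0.80. For selection across parameters, the between-parameter correlation runs from 0 to 0.8. None of these values is in the article.

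**Step 1: optimism at the chosen cut-off.** In 20,000 simulated studies of 20+20 with direction fixed, the cut-off was chosen by maximum J. Apparent J was compared with true J at that same cut-off. Because J = sensitivity + specificity − 1, half of the difference in J is the average excess in each of the two.

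| True AUC | Apparent J | True J at that cut-off | Excess in J | Excess in each (points) |
|---|---|---|---|---|
| 0.5 | 0.174 | 0.000 | 0.174 | 8.7 |
| 0.7 | 0.409 | 0.258 | 0.151 | 7.6 |
| 0.71 (d = 0.8) | 0.428 | 0.278 | 0.150 | 7.5 |
| 0.8 | 0.549 | 0.416 | 0.133 | 6.7 |
| 0.9 | 0.716 | 0.604 | 0.112 | 5.6 |

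How the excess divides between sensitivity and specificity depends on how ties and the position of the cut-off between observations are handled; the total does not.

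**Step 2: stability of the cut-off.** Its standard deviation across repeated studies is about 0.6, 0.5 and 0.4 outcome SD for d = 0.5, 0.8 and 1.2.

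**Step 3: AUC of one parameter, direction preset.** The mean simulated AUC is 0.499, 0.700, 0.800 and 0.900 for true values 0.5, 0.7, 0.8 and 0.9, so there is no bias. For precision, the Hanley–McNeil formula at A = 0.80 uses A/(2 − A) = 0.6667 and 2A²/(1 + A) = 0.7111:

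Variance = [0.80 × 0.20 + 19 × (0.6667 − 0.64) + 19 × (0.7111 − 0.64)] / 400 = 2.018/400 = 0.00504, so SE = 0.071.

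95% CI = 0.80 ± 1.96 × 0.071 = 0.66 to 0.94, which runs from the lowest verbal band to the highest.

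**Step 4: AUC when the best of several is picked.** With direction fixed and every one of 12 parameters at true AUC 0.7, the mean best AUC is 0.76 to 0.83 (correlation 0.8 to 0). With every one at 0.5, it is 0.57 to 0.65. The chance that at least one of 12 uninformative parameters reaches 0.70 is 7 to 17% with direction fixed and 13 to 31% with direction taken from the data. If a curve were drawn for each parameter in each task (12 × 6 = 72), these become 13 to 68% and 25 to 90%. Taking direction from the data lifts even a single uninformative AUC to a mean of 0.575.

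**The case against.** The strongest reply has four parts.

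- *AUC is not affected by the cut-off.* This stands. A reader might infer that the reported AUCs are bound to be optimistic too. The article does not support that: it does not plan to single out a best parameter or task. Its Hypothesis section also sets the direction for refixations (more) and COP displacement (greater), leaving only the COM measures without one.
- *A high chance of spurious discriminators is not established.* This also stands. The answer ranges from 7% to 90% according to the number of curves, their correlation and whether direction is free. The article does not say that ROC curves are drawn by task, and it gives no correlations.
- *This is a condensed article of an exploratory study.* Intervals or internal validation may be in a fuller plan that is not shown, so their absence is no finding. What the article does fix is the cut-off rule and the calculation of sensitivity and specificity, with only these 40 people to use. The exploratory label also sits beside a statement that the thresholds identify the impairment. In mitigation, the Discussion says that results in general, not the cut-offs, will inform later programmes, and that any intervention would be tested in further trials.
- *The band defect is editorial.* Agreed. The value 0.90 falls in two bands, but the ≥ sign settles it. Values between 0.79 and 0.80 have no band only if more than two decimals are used.

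**Conclusion.** The point holds for sensitivity and specificity: followed as written, the plan overstates each by about 6 to 9 points on average, and J by about 0.11 to 0.18, over true AUC 0.9 to 0.5. The size rests on the normal, equal-variance model and the assumed effect sizes. Some upward bias does not depend on them, because a sample maximum is being reported as accuracy. The cut-offs are unstable, and a point AUC cannot be placed reliably in one verbal band. For AUC the risk of optimism is conditional on selecting a parameter, task or direction from the data. This should be fixed; it does not undermine the group comparisons, which do not use the cut-offs.

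**What to change.** - Report sensitivity and specificity corrected for optimism by bootstrap. Each resample should repeat the choice of cut-off and any choice of parameter, task or direction made from the data.
- Set the direction in advance for refixations and COP, where the Hypothesis section gives it.
- Report the ROC results for all parameters analysed, with 95% confidence intervals for AUC and for the cut-off, and give any verbal grade beside the interval.
- Replace the clause saying that the thresholds identify the impairment with a statement that they are hypothesis-generating until tested in an independent sample.
- As a minor edit, make the bands contiguous: ≥0.90, 0.80 to <0.90, 0.70 to <0.80, <0.70.

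The cost is a bootstrap script, some rewording and less favourable figures. No new participants or measurements are needed, and the Results section places the start of data analysis after the article was written. Cutting the ROC step to a few measures on one task would also reduce selection, but it gives up exploratory breadth and is not needed for this correction.

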### Confidentiality

During the screening, the researcher will make note of whether the potential participant meets the study criteria. For those who do not meet the criteria, only the reason for exclusion from the project will be recorded in a database and will not be identifiable.

### Ethics Approval and Consent to Participate

Ethical approval for this study has been obtained from the New Zealand Health and Disability Ethics Committee (HDEC) and Auckland University of Technology Ethics Committee (AUTEC). Eligible potential participants will be asked to provide written informed consent. Ethics committee approval for any protocol modifications will be sought from HDEC and AUTEC. Any changes will lead to an amendment in the Australian New Zealand Clinical Trials Registry (HDEC reference number: 18/CEN/193; AUTEC reference number: 19/38).

### Dissemination of Study Data

A summary of the results from the study will be offered to all participants as per the consent form. Results from the study will be published in a peer-reviewed journal and presented at national and international conferences.

### Availability of Data and Materials

All participants will be given a numerical code upon acceptance into the project. All health information will be stored in physical and electronic records that are identified by the participant code only. Only the named investigators will have access to the forms that contain information about the participant’s name and their code. These forms will be stored in a secured cabinet in co-ordinating investigator’s office, separate from any records containing health information.

The data sets used and analyzed during this study are available from the corresponding author on reasonable request.

## Results

Data collection was started in May 2019 and was completed by February 2020. It was approved by the Institutional Review Board on November 2, 2018 (Ethics ref: 18/CEN/193). We are currently processing the data and will begin data analysis in July 2020. We expect the results to be available for publication by the end of 2020. The trial was funded by the Neurology Special Interest Group, Physiotherapy New Zealand, and the Eisdell Moore Centre in November 2018.

## Discussion

This is an exploratory study with the primary aim to identify whether fixational instability is associated with motion sensitivity and whether it leads to increased postural sway and altered kinematics in adults with motion sensitivity.

This study will provide a detailed investigation of visual fixations, postural sway, and kinematics in complex visual environments. The use of a mobile eye tracker device will investigate naturalistic eye behavior when exposed to experimental stimuli. The task hierarchy will help in understanding how characteristics of visual fixations change when a person views a complex visual environment as opposed to neutral environments. The experimental tasks might provoke symptoms in some participants; however, we expect that all participants will be able to complete the protocol with appropriate rest intervals between tasks. Our sample size of 20 participants in each group is a foundational step in exploring whether visual fixations contribute to motion sensitivity after vestibular disorder. We anticipate the outcomes will be able to detect a difference between healthy adults and those with motion sensitivity. Results from this study will inform future trials and will be used to inform development of diagnostic and rehabilitation programs.

We hope that this study will increase our understanding of the complex interactions of vision and balance in people with motion sensitivity. If we determine that gaze and postural control characteristics are altered, we will develop an intervention that is designed to re-align the gaze and postural control characteristics closer to those of the control population. This intervention would then be tested in a series of clinical trials to determine effectiveness.
